##### Willingness to accept companion video sharing

2.10.2.2

This section assesses the types of smart devices that participants can operate independently, whether they have used smart devices for health monitoring, their acceptance of the concept of mHealth intervention strategies, and their self-assessed ability to use smart devices. It aims to identify factors hindering pregnant women and their companions from using smartphones to capture companion videos for health monitoring. These factors may include privacy concerns related to the videos, reluctance of companions to participate in video recording, and difficulties in operating the video recording process.

##### Adherence to companion video sharing

2.10.2.3

Adherence to the companion video sharing intervention will be assessed based on the frequency and consistency of video sharing by each pregnant woman.

##### Economic indicators

2.10.2.4

Costs incurred during clinic visits, including transportation, examinations, hospitalization, surgery, medication, nutrition, and lost work time.

This study will also collect comprehensive information from participants via an electronic questionnaire, including:

Socio-demographic characteristics such as height, weight, age, education level, marital status, ethnicity, and income;Behavioral characteristics including smoking, drinking, disease history, eating, exercise, and sleeping habits;Maternal pregnancy indicators like pregnancy stage and prior pregnancy experience;History of depression diagnosis and treatment, including past antidepressant use and self-assessed health status;Experience and health knowledge of maternal companions, including previous companion experience and related health knowledge.

### Follow-up

2.11

This study will last for eight months. All participants, both in the intervention and control groups, are required to complete five follow-up assessments: baseline, mid-intervention at 15 weeks of pregnancy, end of intervention at 18 weeks of pregnancy, 36 weeks of pregnancy, and 4 weeks postpartum. The content of these follow-up assessments varies according to the time point. Demographic information is collected only at baseline; behavioral data, clinical test results (such as blood pressure and glucose levels), and questionnaire responses are collected at all follow-up points. Specific details of the information collected at each follow-up are shown in **Table 2**.

**Table 2 T2:** Follow-up Study Table.

Study period	Recruitment	Baseline	Intervention			
Timepoint		0w±1w (T1)	3w±1w (T2)	6w±1w (T3)	24w±1w (T4)	After delivery 4w±1w (T5)
Informed consent	✓					
Random grouping		✓				
Companion video sharing intervention		✓	✓	✓		
Send health-related text or images		✓	✓	✓		
Sociodemographic information		✓				
Behavioral information		✓	✓	✓	✓	✓
Medical history, physical examination (blood pressure, body height, weight, waist circumference), laboratory examinations (blood biochemistry, routine urine test).		✓	✓	✓	✓	✓
EPDS-Dep-5	✓	✓	✓	✓	✓	✓
GAD-7		✓	✓	✓	✓	✓
PSS		✓	✓	✓	✓	✓
PSQI		✓	✓	✓	✓	✓
FSS		✓	✓	✓	✓	✓
FHS-SF		✓	✓	✓	✓	✓
PSSS		✓	✓	✓	✓	✓
CBF-PI-B		✓				

The full name of EPDS-Dep-5 is the simplified version of the Edinburgh Postnatal Depression Scale; The full name of GAD-7 is Generalized Anxiety Disorder scale; The full name of PPS is Perceived Stress Scale; The full name is PSQI is Pittsburgh Sleep Quality Index; The full name of FSS is Fatigue Severity Scale; The full name of FHS-SF is The Family Health Scale short-form; The full name of PSSS is Perceived Social Support Scale; The full name of CBF-PI-B is The Chinese Big Five Personality Inventory Brief Version.

### Statistical methods

2.12

Upon completion of the trial, all collected case data and related questionnaire responses were collated and summarized. Microsoft Office 2016 was utilized for data storage; statistical analysis was conducted using SPSS Statistics 27.0 software. Count data were presented as both the number of cases (N) and percentage (%). Continuous data distribution was assessed for normality. Normally distributed data were expressed as mean ± standard deviation, whereas non-normally distributed data were presented as median (IQR, P25–P75). Baseline characteristics between the intervention and control groups were compared and analyzed using appropriate statistical tests. The choice of tests—including two independent samples t-test, Mann-Whitney U-test, and chi-square test—depended on the nature of the data. Longitudinal analysis of follow-up data was conducted using Generalized Estimating Equations (GEE) to compare differences in indicators between the intervention and control groups. A two-sided test was employed, with statistical significance set at the *P* < 0.05.

Regarding missing data, multiple imputation techniques were employed, justified by the missing at random (MAR) nature of the missing data. Multiple imputation involves generating multiple filled datasets by replacing missing values with reasonable estimates derived from observed data and imputation models. This method reflects the uncertainty of missing data, maintains dataset variability, and enhances result reliability compared to single imputation methods. Multiple imputation methods were implemented using established statistical packages such as SPSS or R. Sensitivity analyses were also performed to assess result robustness under various missing data assumptions. Therefore, this comprehensive approach ensures the validity and reliability of the study findings, accounting for missing data while maintaining statistical integrity throughout the analysis process.

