### Sample size

2.5

This study is a randomized controlled trial with an intervention group using companion video sharing and a control group receiving usual care. The primary outcome indicator observed is the EPDS score of the study population. Based on a previous intervention study (52), the EPDS score of the intervention group was 12.0 at 36 weeks’ gestation, while the control group had a score of 14.9 at the same gestational age. We set the hypothesis certainty (1-β) at 90%, and the significance level (α) at 0.05. Using PASS 15.0, the calculated sample size for the study was 32 participants, with 16 in the companion video sharing group and 16 in the traditional care group. Considering a 20% attrition rate, 40 participants were included in the study.

Group sample sizes of 20 and 20 achieve 99.472% power to reject the null hypothesis of equal means when the population mean difference is μ1 - μ2 = 12.0 - 14.9 = -2.9 with standard deviations of 2.4 for group 1 and 1.4 for group 2, and with a significance level (alpha) of 0.050 using a two-sided two-sample unequal-variance t-test.

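### Section 2.12 tests baseline differences between randomised arms but does not say whether or how the T1 EPDS-Dep-5 score enters the GEE; it should be a pre-specified covariate

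*Protocol article*

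**What the plan says.** Protocol article, section 2.12 (Statistical methods), states one use of baseline data outright: "Baseline characteristics between the intervention and control groups were compared and analyzed using appropriate statistical tests". The tests named are the two-sample t-test, the Mann-Whitney U-test and the chi-square test. The same section then gives GEE as the longitudinal method for comparing the arms. It lists no model terms: no visit effect, no interaction, no covariate, and no statement of how the T1 value is handled.

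Section 2.11 (Follow-up) counts baseline as one of the follow-up assessments: "All participants, both in the intervention and control groups, are required to complete five follow-up assessments: baseline, mid-intervention at 15 weeks of pregnancy". Table 2 ticks EPDS-Dep-5 at recruitment and at T1 to T5. It also ticks the anxiety, stress, sleep, fatigue, family health and social support scales at T1 to T5.

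Section 2.6.1 specifies simple randomisation and mentions no stratification by severity. Section 2.4.1 requires a screening EPDS-Dep-5 score of at least 4. Section 2.5 plans 32 evaluable women and 40 enrolled.

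**The concern.** There are two linked problems.

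- **The baseline tests.** Allocation is random, so any baseline difference between arms is due to chance, and a test of whether it is due to chance answers no question. In a trial this small, a non-significant result also gives false reassurance, because sizeable imbalances go undetected.
- **The open GEE specification.** The baseline score of the primary outcome is usually among the strongest predictors of the later score. The text can be read as a GEE on post-baseline visits without T1, or as a GEE in which T1 is one more repeated outcome. These readings give different estimators with different precision, and both are less precise than adjusting for T1.

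At stake is the width of the confidence interval in a 40-woman trial. Under the first reading, an unlucky split in starting severity also shifts the observed effect.

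**Working it through.** **Plan's own figure.** Section 2.5 uses "the population mean difference is μ1 - μ2 = 12.0 - 14.9 = -2.9", "with standard deviations of 2.4 for group 1 and 1.4 for group 2", and computes power "with a significance level (alpha) of 0.050 using a two-sided two-sample unequal-variance t-test". At 20 per arm, SE = √(2.4²/20 + 1.4²/20) = √0.386 = 0.621 and the noncentrality is 2.9/0.621 = 4.67. Power from the noncentral t with Satterthwaite degrees of freedom is 99.472%, as printed. Also 32/(1 − 0.20) = 40, as printed. The calculation compares two means and takes no credit for baseline adjustment.

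**Chance imbalance.** With n per arm, the baseline difference has SE √(2/n) in SD units, which is √(2/20) = 0.316 at n = 20.

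- P(|difference| > 0.3 SD) = 2[1 − Φ(0.3/0.316)] = 34%.
- P(|difference| > 0.5 SD) = 2[1 − Φ(0.5/0.316)] = 11%.
- An observed 0.5 SD difference gives t = 0.5/0.316 = 1.58, p about 0.12. A baseline test would therefore pass over it. Significance needs about 1.96 × 0.316 = 0.62 SD.

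**Carry-over if T1 is left out.** The part passed into the follow-up difference is about r times the imbalance. For 0.5 SD this is 0.15 SD at r = 0.3 and 0.35 SD at r = 0.7.

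**Precision.** Take one follow-up visit, equal SDs at T1 and follow-up, and baseline-to-follow-up correlation r. The variance factors relative to 2σ²/n are:

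- post-only: 1
- change score: 2(1 − r)
- covariate adjustment: 1 − r²

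So adjusted/change = (1 − r²)/[2(1 − r)] = (1 + r)/2.

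| assumed r | change score / post-only | adjusted / post-only | adjusted / change score |
|---|---|---|---|
| 0.2 | 1.60 | 0.96 | 0.60 |
| 0.3 | 1.40 | 0.91 | 0.65 |
| 0.5 | 1.00 | 0.75 | 0.75 |
| 0.7 | 0.60 | 0.51 | 0.85 |

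**Small-sample cost.** Estimating the slope inflates the adjusted variance on average by 1 + 1/(2n − 4): 1 + 1/36 = 1.028 at 20 per arm and 1 + 1/28 = 1.036 at 16. At r = 0.2 the factor against post-only becomes 0.96 × 1.028 = 0.99, so almost no gain is left. At r = 0.5 it is 0.75 × 1.028 = 0.77.

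The planning SDs belong to EPDS means of 12.0 and 14.9, whereas five items scored 0 to 3 have a maximum of 15. For that reason, imbalance is given in SD units and precision as ratios, not in points.

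**The case against.** A reader might infer that baseline EPDS-Dep-5 is used only in the between-arm tests and that the GEE is unadjusted. The article does not say so. It names no GEE terms at all, and a condensed article commonly leaves a covariate list to a full protocol or analysis plan, neither of which is shown. Silence on covariates is not a statement that there are none.

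A reader might also infer that chance imbalance certainly contaminates the estimate. Section 2.11 counts baseline among the five assessments, so a GEE with T1 as a repeated outcome is a plausible reading, and with free group-by-time terms that contrast subtracts the baseline difference. A longitudinal model that constrains the arms to a common T1 mean would be about as efficient as covariate adjustment. Nor is imbalance a systematic bias: over repeated randomisations it adds random error.

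The gain is uncertain too. No correlation is given, T1 to T4 spans 24 weeks, and the entry cut may weaken the correlation. At the planned effect, power is already above 99% at 20 per arm, so adjustment adds little there. Baseline tests in a descriptive table do not change the effect estimate, and nothing says that they select covariates.

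All of this stands, and it limits the point. It does not remove it. The baseline tests are stated in the text, the two plausible GEE readings differ materially, and adjustment is at least as good as the more favourable of them at almost no cost.

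**Conclusion.** The point holds as a recommendation to specify the model, not as proof of an unadjusted analysis. The baseline significance tests are stated in the text and are uninformative. Whether and how T1 enters the GEE is left open.

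Against a post-only GEE, adjustment saves 4% of the variance at r = 0.2 (about 1% after the cost of estimating the slope), 9% at 0.3, 25% at 0.5 and 49% at 0.7. Against a GEE with the arms free to differ at T1, it saves 40%, 35%, 25% and 15% at the same correlations, before the slope cost. These savings rest on assumed correlations, one follow-up visit at a time, and equal SDs at T1 and follow-up for the change-score comparison. The imbalance probabilities rest on 20 per arm and approximate normality. The benefit would show mainly in interval width and at effects smaller than the planned one.

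**What to change.** In section 2.12:

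- State that the GEE models the post-baseline visits T2 to T5 with the T1 EPDS-Dep-5 score as a pre-specified covariate.
- Do the same for each repeated secondary scale, using its own T1 value.
- Replace the between-arm baseline tests with a descriptive table without P values.

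The cost is two or three sentences and no new data. The main baseline term uses one degree of freedom. A baseline-by-visit interaction uses more and should be optional, since there are only 32 to 40 clusters. If a fuller protocol or analysis plan already fixes the handling of T1, section 2.12 should state that choice.

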### Trial design

2.2

This study adopts a randomized controlled trial design and is conducted at Dongying People’s Hospital, Shandong Province, China. The intervention involves family support-based companion video sharing among perinatal women and their families. Forty participants are randomized into two groups: a 20-participant intervention group receiving companion video sharing and a 20-participant control group receiving traditional care. The research flowchart is shown in **Figure 1**.

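### GEE is the only between-group longitudinal method named for 40 women, with no small-sample provision; in its usual sandwich Wald form it would exceed the nominal 5% level

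*Protocol article*

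**What the plan says.** Section 2.12 (Statistical methods) of the protocol article gives the efficacy analysis in one sentence: "Longitudinal analysis of follow-up data was conducted using Generalized Estimating Equations (GEE) to compare differences in indicators" between the two arms. The level follows: "A two-sided test was employed, with statistical significance set at the" 0.05 threshold. On software it says "statistical analysis was conducted using SPSS Statistics 27.0 software"; R is mentioned only as an option for multiple imputation. The section does not state the variance estimator, reference distribution, working correlation or tested contrast.

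Section 2.2 (Trial design) fixes the number of independent subjects: "Forty participants are randomized into two groups: a 20-participant intervention group receiving companion video sharing and a 20-participant control group receiving traditional care". Section 2.5 (Sample size) gives the number before the attrition allowance, "the calculated sample size for the study was 32 participants, with 16 in the companion video sharing group and 16 in the traditional care group", and then "Considering a 20% attrition rate, 40 participants were included in the study". Its planning targets are "We set the hypothesis certainty (1-β) at 90%, and the significance level (α) at 0.05". The power statement there rests on an unequal-variance t-test of EPDS means at 36 weeks of gestation, not on GEE. Section 2.11 (Follow-up) lists five assessments per woman, baseline included.

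**The concern.** The standard GEE result is asymptotic in the number of independent subjects, here the women and not their visits. With 16 to 20 women per arm, the plain sandwich variance is biased downward, because residuals are measured around means fitted to the same few women. A normal or chi-square reference also ignores the uncertainty in that variance. Both effects make P values too small, and the second grows with the number of parameters tested jointly.

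The planning calculation in section 2.5 used a t-test, which has small-sample degrees of freedom. Its 5% level does not carry over automatically to a GEE Wald test. At stake is whether a positive result would have the false-positive rate that the article states. Section 3 (Discussion) expects the results to support wider use of mobile health interventions and to inform policy.

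**Working it through.** **Inputs from the article.** 20 women per arm (2.2); 16 per arm before the attrition allowance (2.5); 20% attrition (2.5); five assessments (2.11); two-sided 5% (2.12); means 12.0 and 14.9, SDs 2.4 and 1.4 (2.5).

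**Assumptions for the size calculation.** Identity link, balanced complete data, normal outcomes, and a separate mean for each group and visit. Under these the closed-form sizes do not depend on the within-woman correlation. The simulations assume a correlation of 0.5.

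**Step 1: the plan's own figures.**
- Attrition: 32 / (1 − 0.20) = 40. This agrees.
- Power at 20+20: standard error = √(2.4²/20 + 1.4²/20) = √0.386 = 0.621; noncentrality = 2.9 / 0.621 = 4.67; Welch degrees of freedom = 30.6; power = 99.47%. The stated 99.472% reproduces.

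**Step 2: one contrast (1 df), plain sandwich, normal reference.** With n women per arm, the sandwich variance equals the unbiased variance times (n − 1)/n. The Wald test therefore rejects when |t| with 2n − 2 df exceeds 1.96 × √((n − 1)/n).
- n = 20: cutoff 1.96 × √0.95 = 1.910; P(|t| > 1.910) on 38 df = 6.4%.
- n = 16: cutoff 1.96 × √0.9375 = 1.898; P(|t| > 1.898) on 30 df = 6.7%.

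**Step 3: joint group-by-visit test (4 df), plain sandwich, chi-square reference.** The chi-square cutoff is 9.488. The test rejects when Hotelling's T² exceeds 9.488 × (n − 1)/n. With ν = 2n − 2, F = T² × (ν − 3)/(4ν) on 4 and ν − 3 df.
- n = 20: T² cutoff 9.013; F = 9.013 × 35/152 = 2.075; P(F > 2.075) on 4 and 35 df = 10.5%.
- n = 16: T² cutoff 8.895; F = 8.895 × 27/120 = 2.001; P(F > 2.001) on 4 and 27 df = 12.3%.

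**Step 4: simulation under no effect, five visits.**

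| Setting | 1 df | 4 df |
|---|---|---|
| Independence GEE, normal data, 20+20 (10,000 runs) | 6.5-6.7% | 10.9% |
| Same, 16+16 | 6.7-6.8% | 11.9% |
| Same, 14+18 | 6.3-6.8% | 12.7% |
| Same, SDs 2.4 and 1.4, 20+20 | 6.4% | 11.6% |
| Same, SDs 2.4 and 1.4, 16+16 | 6.7% | 13.4% |
| Same, skewed data, 20+20 | 5.9% | 9.0% |
| Exchangeable GEE, simple randomization, 40 women (1,000 runs) | 5.8% | 8.7% |
| Same, 32 women | 6.4% | 13.4% |
| Model-based variance, correct working correlation, 40 women (1,500 runs) | 5.0% | 5.2% |
| Same, 32 women | 5.9% | 5.3% |

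**Step 5: size after correction (20+20 and 16+16, normal data).**
- Mancl-DeRouen variance with the usual normal or chi-square reference: 5.1-5.5% (1 df), 8.4-8.6% (4 df). With SDs 2.4 and 1.4 the 4-df figure is 8.7-9.6%.
- Mancl-DeRouen variance with a t reference on N − 2 df: 4.4-4.7% (1 df).
- Mancl-DeRouen variance with a Hotelling-type F reference: 4.0-4.6% (4 df).

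For the joint test, correcting the variance alone is not enough; the reference distribution must change too.

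**The case against.** The strongest objection is that the defect is read into silence. Section 2.12 mentions no sandwich variance, Wald test or group-by-visit term, and it does not say that the analysis is uncorrected. An article commonly leaves such details to a fuller protocol or analysis plan, which is not shown here. A reader might infer that the trial's 5% level is already lost. The documents do not support that: a model-based variance with a correct working correlation gives about 5-6%, and a corrected test stays just under 5%. This part of the objection stands and makes the point conditional.

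A reader might also take 10-12% as the error rate of the main efficacy test. That is not supported either. The article does not name a joint test, and the only effect it sizes, in section 2.5, is a difference at 36 weeks. That is a single contrast, for which the excess is modest.

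Multiple imputation is planned, so up to 40 women could enter the analysis. The 16+16 figures are then the pessimistic end of the range, and skewed scores reduce the excess further.

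Finally, GEE does not have to be abandoned. An unstructured covariance over five visits has 15 parameters, a real load for 32 to 40 women, so a mixed model of that kind is an option and not a necessity.

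What remains is more than a missing detail. The article does name a large-sample method for a 40-woman trial, and that method run in its usual form gives P values that are too small.

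**Conclusion.** The point holds in conditional form. If GEE is run with the plain sandwich variance and a normal or chi-square Wald reference, the true two-sided size at nominal 5% is about 6.4% (20+20) to 6.7% (16+16) for one visit contrast. For a joint 4-df group-by-visit test it is about 10.5% to 12.3%, roughly double the nominal level. The single-contrast excess is small; the joint-test excess is material.

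These figures assume an identity link, complete balanced data and normal outcomes; no imputation step was modelled. Confidence is high in the arithmetic and limited as to which form of GEE the trial will run, because the article does not say.

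**What to change.** In section 2.12, keep GEE and state three things in advance:

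1. **Variance:** a bias-corrected sandwich, for example Mancl-DeRouen.
2. **Reference distribution:** t for single contrasts and F for joint tests, with small-sample degrees of freedom. This must accompany the variance correction.
3. **Primary comparison:** the group contrast at 36 weeks, the time point that section 2.5 sizes.

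Use the same variance and reference for the secondary scales. A REML mixed model with Kenward-Roger or Satterthwaite degrees of freedom is an acceptable alternative, not a requirement.

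The cost is one paragraph and no new data. Intervals become slightly wider and P values larger. The correction may need software other than SPSS, such as R, which section 2.12 already mentions for imputation.

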### Study management

2.13

#### Data collection

2.13.1

All study participants will complete corresponding questionnaires at baseline and during follow-up visits. The Questionnaire Star platform will provide the online questionnaires via a QR code, which participants will scan to complete them. Additionally, pregnant women sociodemographic and behavioral information will be collected using the same method through the case system and self-designed questionnaires.

#### Storage and archiving of data

2.13.2

The investigators stored all research-related data (e.g., baseline and follow-up questionnaires, randomization records, follow-up information lists) and documents (e.g., subject informed consent forms, shared accompanying video files) in a standardized format within a dedicated research database. Following trial completion, all source data and documents were archived in compliance with applicable laws and regulations. Access to the database required investigator permission, with mandatory registration of visitor details and access purpose to prevent unauthorized access and data misuse (68).

